## Abstract

**Background:**

The benefits of physical activity (PA) and adequate sleep are well documented, and their importance strengthens with the increasing prevalence of chronic diseases and multimorbidity (MM). Interventions to promote physical activity and sleep that use commercial activity trackers may be useful non-pharmacological approaches to managing individual health; however, limited evidence exists on their use to improve physical activity in older adult patients with MM.

**Methods:**

This study aims to measure the effects of behavioral change techniques (BCTs) delivered by a wearable device on physical activity and quality of sleep (QS) in older adult patients with MM. We designed an open-label randomized controlled trial with participants recruited through primary care and a specialist outpatient clinic. Participants must be more than 65 years old, have MM, and have access to smartphones. All eligible participants will receive PA promotion content and will be randomly assigned to wear a smartwatch. The primary outcome will be the participants’ PA measurement at baseline and at six months using the International Physical Activity Questionnaire - Short Form (IPAQ-SF). Secondary outcomes will include changes in the participants’ frailty status, biometric measurements, quality of life, and biopsychosocial assessments. A sample size of 40 participants per arm was calculated to detect group differences, with 50 participants planned to recruit and randomize into each arm.

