## Methods/Design

### Aims of the study

The main purpose of this study is to measure the effect of the use of BCTs delivered by a wearable device in addition to an intervention to promote PA and quality of sleep (QS) in reported activity by an older adult population with MM. We also aim to assess PA measurements experienced by patients with MM, their relationship with patient-reported outcomes, and adverse clinical outcomes.

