### Study intervention

All Participants who are eligible and consented to participate in the study shall receive PA promotion content in accordance to the Swedish model [23]. This method consists of five core components: (1) person-centered health promotion consultation; (2) a written prescription of physical activity; (3) a prescription guided by evidence-based knowledge on physical activity in the prevention and treatment of health conditions; (4) a follow-up of the written prescription; and (5) collaboration between the healthcare service and physical activity organizers outside healthcare. It is also emphasized that the method should be tailored to the local conditions in healthcare organizations. More specifically, we will recommend PA and provide informative flyers according to the Portuguese National Healthcare Authority and the World Health Organization recommendations for older age people. In addition to PA promotion counseling, all patients will be randomly allocated to either the intervention or the control groups using block randomization generated by a computer-generated random number sequence^1^. The allocation sequence will be generated by a research assistant who will not be involved in the data collection process. Eligible participants will be randomly assigned in a 1:1 ratio to one of the following intervention arms: Arm A (experimental arm), use of the device activity watch (Fitbit Sense), and a sleep monitoring mattress (Withings SA, France - Sleep Analyzer); Arm B (control): non-use of the devices. Participants randomized to wearable device BCT (Arm A) will be provided goal setting, self-monitoring and feedback. On the first visit they will undergo a brief training session where they’ll learn how to effectively use both devices, sync their data, and interpret the feedback they receive. Arm A participants will receive weekly feedback based on their activity and sleep data trough their devices. This might include suggestions for increasing step counts or tips for better sleep hygiene. The study team will provide a communication channel available for participants to address any technical issues or queries they might have regarding device usage. They will be instructed to wear the wearable device all the time (except when charging) and use the mattress while sleeping. Patients who do not use the device for at least 60% of the time will be excluded from the trial. Compliance of divide use will be regularly monitored by the study team.

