### Study measures and outcomes

All participants will have two study visits: baseline and after 6-month follow-up (Fig. 1). Measurements will include self-reported data: IPAQ-SF, INTERMED-Self Assessment (IMSA) and Short Form Health Survey (SF-12); study team measurements: Vivifrail test^2^, Body Mass Index (BMI), abdominal perimeter and calf perimeter measurements; and Electronic Health Records (EHRs) information retrieval (diagnoses, medications, and unplanned health visits before and during the study period). Information on the treatment allocation will not be provided to the data collectors. The data collection forms only contain unique identifier codes assigned to each participant.

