**Fig. 1 Fig1:**
[figure not shown]
SPIRIT diagram

The primary outcome will be the participants’ PA measurement assessed at baseline and at 6 months using the IPAQ-SF. Secondary outcomes will include changes in participants’ frailty status, biometric measurements, quality of life, and biopsychosocial assessments at baseline and at 6 months (Table 1).

**Table 1 Tab1:** Data measurements to be recorded during the study period

	Baseline	Study period	6 month follow-up
**Self-reported**	IPAQ-SF		IPAQ-SF
	IMSA		IMSA
	SF-12		SF-12
**Healthcare professional reported**	Vivifail questionnaire		Vivifail questionnaire
	BMI		BMI
	Abdominal perimeter		Abdominal perimeter
	Calf perimeter		Calf perimeter
**Sensor data**		Number of steps	
		Heart rate	
		Sleep quality	
**EHR data**	Historical clinical data	Unplanned hospital admissions	

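### The abstract promises an effect on sleep quality, but sleep is recorded only by devices that the control arm does not use

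*Protocol article*

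**What the plan says.** - **Aim, abstract (Methods).** The study is to measure the "effects of behavioral change techniques (BCTs) delivered by a wearable device on physical activity and quality of sleep (QS") in older patients with multimorbidity. The next sentence describes a randomised controlled trial.
- **Aim, main text (Aims of the study).** The effect is that of device-delivered techniques "in addition to an intervention to promote PA and quality of sleep (QS) in reported activity by an older adult population with MM". Here sleep is attached to what is being promoted, and the effect appears to be located in reported activity.
- **Devices (Study intervention).** Arm A gets an activity watch and a sleep-monitoring mattress. The comparator is "Arm B (control): non-use of the devices". For Arm A, "On the first visit they will undergo a brief training session" on both devices, feedback on activity and sleep data is weekly, and "They will be instructed to wear the wearable device all the time (except when charging) and use the mattress while sleeping".
- **Measures (Study measures and outcomes).** "Measurements will include self-reported data: IPAQ-SF, INTERMED-Self Assessment (IMSA) and Short Form Health Survey (SF-12"). The study team adds the Vivifrail test, BMI, and abdominal and calf perimeter, and health-record data are retrieved. In Table 1, "Sleep quality" appears once, under sensor data in the study-period column. Its baseline and 6-month cells are empty.
- **Outcomes.** The primary outcome is physical activity by IPAQ-SF. The secondary outcomes are changes in "frailty status, biometric measurements, quality of life, and biopsychosocial assessments at baseline and at 6 months".
- **Statistical analysis.** No comparison of sleep is named.

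**The concern.** A randomised effect on an outcome is a contrast between arms, so the same outcome has to be observed in both. For sleep, the instrument that would measure the outcome is also the intervention, and the control arm is defined by not having it. The sleep part of the abstract's aim then has no control data behind it.

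Arm A alone cannot stand in. Its sensor record begins after device training, so there is no untreated baseline from which to measure change. Comparing early with late nights in Arm A is possible, but it is uncontrolled and entirely on treatment. It could not separate the devices from the activity promotion that both arms receive, from season, or from regression to the mean.

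At stake is a stated aim that the trial cannot meet, although the intervention includes a dedicated sleep mattress and feedback on sleep.

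**Working it through.** **The plan's own figure.** The Statistical analysis section gives 40 per arm and 20% dropout. 40 / (1 − 0.20) = 50 per arm, which matches the stated 50. The base figure of 40 cannot be re-derived because the article gives no effect size or standard deviation, but nothing here depends on it.

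**Measures taken at both visits (Table 1).** IPAQ-SF, IMSA, SF-12, Vivifrail, BMI, abdominal perimeter, calf perimeter: 7 measures, of which 0 are presented as a sleep measure.

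**Outcomes listed.** Physical activity (primary), then frailty, biometrics, quality of life and biopsychosocial assessment (secondary): 1 + 4 = 5 outcomes, of which 0 are sleep.

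**Scheduled sleep data by arm and time**, from Table 1 and the Study intervention section:

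| | Arm A | Arm B |
|---|---|---|
| Before the intervention | 0 of 50 | 0 of 50 |
| During the intervention (sensors) | up to 50 of 50; 50 × 0.80 = 40 after dropout | 0 of 50 |
| Questionnaire or other sleep measure at 6 months | none listed | none listed |

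The between-arm sleep effect is the Arm A mean minus the Arm B mean on a common measure. The second term has no observations, so the difference cannot be estimated at any sample size. The within-arm change from an untreated baseline lacks its first term, so it cannot be estimated either.

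**Could the first nights in Arm A serve as a baseline?** The article does not give the date of the first feedback. Assume 6 months is 26 weeks and the first feedback comes after one week. There are then 26 × 7 = 182 nights, of which 7 precede feedback: 7 / 182 = 3.8%. Those nights already follow the training session and are spent with the devices in use, so they are not untreated. This is a side point, because the absence of any Arm B value settles the randomised comparison.

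**The case against.** The strongest reply is that the contradiction rests on one phrase in an abstract. The section on aims can be read as placing the effect in reported activity only, with sleep as part of what is promoted. Much else fits that reading: the primary outcome is IPAQ-SF, the Discussion speaks of activity patterns, and no sleep comparison is planned. On that view the abstract is loosely worded and the design is sound. The ambiguity is real. However, if the narrower aim is the intended one, the abstract misstates it and needs correcting, so some change is required on either reading.

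A second reply is that this is a condensed article. The lists of measures and secondary outcomes are introduced in non-exhaustive terms, the SPIRIT figure is not shown, the local registry of patient-reported outcomes is not itemised, the item content of IMSA and SF-12 is not given, and health records could hold sleep diagnoses. This stands as a limit on wording: the supported statement is that no control-arm sleep measure is listed, not that none could exist anywhere. It does not remove the point. Table 1 sets out the data to be recorded by time point, none of these sources is offered as a measure of sleep quality, and an analysis plan cannot supply control data that were not collected.

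A third reply is that little follows, because no stated endpoint, test or sample size changes. That is correct, and it keeps the point below the level of a threat to the primary analysis.

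**Conclusion.** The concern holds. As written, the trial cannot estimate the effect on sleep quality that its abstract sets out to measure: scheduled sleep data exist in 1 of 2 arms, only on treatment, with 0 of 50 pre-intervention values in each arm.

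The conclusion rests on two readings. The first is that the abstract's sentence makes sleep an object of the effect, which is its plain grammar. The second is that Table 1 and the list of measures are complete as far as sleep is concerned. It does not touch the physical activity comparison or the primary outcome, and the plan does not announce any conclusion about sleep. The mismatch should be corrected: it makes one stated aim unattainable and leaves the main comparison intact.

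**What to change.** **Preferred.** Add one short validated self-report sleep questionnaire, completed by both arms at the baseline and 6-month visits. List it under Study measures and outcomes and in Table 1, name it as a secondary outcome, and compare the arms at 6 months with adjustment for the baseline score. Keep the watch and mattress sleep data as descriptive information on Arm A. The cost is one short form at two visits that already take place, for 100 participants. It carries the open-label reporting bias that the trial already accepts with IPAQ-SF. The form has to be in use before the first visit, since a baseline score cannot be recovered afterwards.

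**Alternative, wording only.** Remove sleep quality from the comparative aim in the abstract, reword the Aims of the study so that reported activity is plainly the only measured effect, label the Arm A sensor sleep data as descriptive, and state that no effect on sleep will be claimed. The price is giving up the sleep aim.

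Giving the mattress to Arm B would supply an objective measure in both arms, but it would expose the controls to part of the intervention, so it is not recommended.

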**Discussion:**

This study aims to contribute to a better understanding of PA patterns and the impact of wearable-based PA interventions in patients with MM. In addition, we aim to contribute to more knowledge about the relationship between PA patterns, Patient Reported Outcomes Measures (PROMs), and healthcare resource utilization in patients with MM. To achieve this, the study will leverage a locally developed PROMs registry and assess data from participants’ medical records, in order to understand the added impact of wearable data and medical information data on predicting PROMs and unplanned hospital admissions.

**Trial registration:**

NCT05777291

**Supplementary Information:**

The online version contains supplementary material available at 10.1186/s12877-023-04511-y.

## Background

Concurrently, the harmful effects of physical inactivity, which refers to the level of Physical Activity (PA) that fails to meet the guidelines, and the benefits of meeting these guidelines are well established [1–3]. PA and exercise, the latter being a planned, structured, repetitive version of physical activity that promotes physical fitness maintenance or development, are key components of lifestyle medicine [1]. The benefits of PA and exercise extend beyond improving mental health and quality of life and contribute to the prevention and treatment of several chronic diseases, including but not limited to obesity, cardiovascular conditions, diabetes, and various types of cancer [4–6].

Lack of sleep has been suggested to play a significant role in the development of major non-communicable diseases (NCDs), which motivates sleep habits to be considered an important modifiable health risk factor and a key component of a healthy lifestyle [7]. Additionally, most manifestations of NCDs worsen with age [8]. As part of lifestyle medicine, further changes in PA and sleep may constitute useful non-pharmacological approaches to managing individual health in older adults [9, 10]. While some aspects of behavior change are still not fully understood, the effectiveness of behavioral change techniques (BCTs) in both altering and sustaining health behaviors, including physical activity and sleep, has been proven, even among the geriatric population [11, 12].

Activity monitoring bracelets, smartwatches, and other wearables may serve as convenient delivery channels for these BCTs and could assist older adult patients in implementing the previously mentioned changes [13, 14]. A recent systematic review showed strong evidence of the positive impact of wearables on increasing physical activity among the general population, although effect on physiological and psychosocial measures was not clear [15]. Despite these findings, limited evidence exists on older adult patients with multimorbidity, both on objectively measured PA as well as on the efficacy of using activity trackers to improve PA [16]. Commercial off-the-shelf activity trackers allow users to self-monitor their daily PA, including the number of steps, type of PA, and amount of sleep. Fitbit (Fitbit Inc, San Francisco, CA, USA) activity trackers have previously been utilized as both measurement and intervention tools, however, it is unclear how they are being integrated into PA intervention studies, and their use in Multimorbidity (MM) patients remains limited [16, 17]. Moreover, in order to access the impact of the PA the patient’s view must be considered. This can be measured using PROMs which are often not considered in these studies [18, 19].

## Methods/Design

### Aims of the study

The main purpose of this study is to measure the effect of the use of BCTs delivered by a wearable device in addition to an intervention to promote PA and quality of sleep (QS) in reported activity by an older adult population with MM. We also aim to assess PA measurements experienced by patients with MM, their relationship with patient-reported outcomes, and adverse clinical outcomes.

### Design and setting of the study

This study will be an open-label randomized control trial, reported in line with the Consolidated Standards of Reporting Trails (CONSORT) statement and checklist and Template for Intervention Description and Replication (TIDieR) checklist [20, 21]. Participants will be recruited through primary care and specialist outpatient clinic at Hospital da Luz Lisboa, a private tertiary hospital in Lisbon, Portugal.

### Inclusion and exclusion criteria

Patients may be included if they are more than 65 years old and have MM. We will use a previously proposed definition of MM as the presence of two or more of the following chronic conditions: hypertension, depression or anxiety, chronic musculoskeletal conditions causing pain or limitation, arthritis and/or rheumatoid arthritis, osteoporosis, asthma, chronic obstructive pulmonary disease (COPD), ischemic heart disease, peripheral artery disease, heart failure, cerebrovascular diseases, chronic stomach or colon conditions, chronic hepatitis, diabetes mellitus, thyroid disorders, any active cancer in the previous five years, chronic kidney disease, chronic urinary conditions, hyperlipidemia, and obesity [22]. In addition, participants must have access to their smartphones. Exclusion criteria will include: patients who are sufficiently physically active, defined with International Physical Activity Questionnaire - Short Form (IPAQ-SF) > 150 min aerobic physical activity per week, an existing absolute contraindication for PA according to the American College of Sports Medicine (acute myocardial infarction within two days, ongoing unstable angina, uncontrolled cardiac arrhythmia with hemodynamic compromise, active endocarditis, symptomatic severe aortic stenosis, decompensated heart failure, acute pulmonary embolism, pulmonary infarction, deep venous thrombosis, acute myocarditis or pericarditis, acute aortic dissection, physical disability that precludes safe and adequate testing), poor comprehension of Portuguese language, disabling neurological disorder (defined as mRankin score $$\ge$$ 4), severe psychiatric illness, learning disability, dementia and cognitive impairment, registered blind, housebound or resident in a nursing home, non-ambulant, advanced cancer, and scheduled for surgery within five months after the first consultation. Orthopedic or rheumatologic diseases with severe impairment and chronic pain syndromes with inherently reduced mobility will also not be included.

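### Entry requires only smartphone access, device workability is tested in Arm A alone after allocation, and the 60% use rule can then remove patients from that arm only

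*Protocol article*

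**What the plan says.** Under Inclusion and exclusion criteria the protocol article states: "In addition, participants must have access to their smartphones". The Abstract's Methods paragraph is no stricter: "Participants must be more than 65 years old, have MM, and have access to smartphones". Neither mentions compatibility with the device apps, a test pairing or the ability to operate the devices. The same section does exclude, in both arms, poor comprehension of Portuguese and "severe psychiatric illness, learning disability, dementia and cognitive impairment, registered blind".

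The Study intervention section sets the sequence. Eligibility comes first: "Eligible participants will be randomly assigned in a 1:1 ratio to one of the following intervention arms". Only Arm A receives the watch and the mattress; the comparator is "Arm B (control): non-use of the devices". Device support is likewise for one arm: "Participants randomized to wearable device BCT (Arm A) will be provided goal setting, self-monitoring and feedback". Of these Arm A participants it says: "On the first visit they will undergo a brief training session where they’ll learn how to effectively use both devices, sync their data". A communication channel for technical problems and regular monitoring of compliance are also described. The section then adds: "Patients who do not use the device for at least 60% of the time will be excluded from the trial".

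**The concern.** The intervention is digital delivery: two devices from different makers, synced data and weekly feedback over six months, in people over 65. Having a smartphone does not show that this can be delivered. An outdated phone, or a user who cannot manage syncing, passes the criterion in both arms but can be discovered only in Arm A.

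Discovery in one arm is not in itself a bias. If everyone is analysed as randomised, it is non-adherence and costs power. The 60% rule makes it more serious, because Arm B has no device whose use could fall short. Patients removed after randomisation would then be selected partly on digital ability, which may be related to age, frailty and activity. The arms would no longer be the groups that randomisation created.

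**Working it through.** **Sequence, from the protocol article**

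| Step | Arm A | Arm B |
|---|---|---|
| Smartphone criterion before allocation | access only | access only |
| Cognitive, visual and language exclusions before allocation | applied | applied |
| Learning to use and sync the devices, after allocation | yes | no |
| Exclusion below 60% device use | can apply | cannot apply |

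The first two rows treat the arms alike. The last two do not, and no printed step before allocation would reveal an unworkable phone or user.

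**The plan's own figure**

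Statistical analysis gives 40 per arm, alpha 0.05, power 0.80 and 20% dropout. 40 / (1 - 0.20) = 50, which matches the planned 50 per arm. The 40 itself cannot be reproduced, because no effect size, SD or event rate is stated.

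**Implied effect (assumption: comparison of two means, two-sided alpha 0.05)**

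d = (1.960 + 0.842) x sqrt(2/40) = 0.626. With one-sided alpha it would be 0.556; the two-sided value is used below.

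**Further assumptions**

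- A fraction f of Arm A cannot run the devices. The documents give no value; the range shown is 5-15%.
- 40 per arm are otherwise evaluable, so these failures come on top of the planned dropout.
- Outcome SD is 1 and the normal approximation holds.

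**(a) Failures kept, with no device effect**

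The mean difference becomes d(1 - f). Power = Phi[d(1 - f) / sqrt(2/40) - 1.960]. For f = 0.15: 0.626 x 0.85 = 0.532; 0.532 / 0.2236 = 2.381; Phi(0.421) = 0.663.

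**(b) Failures excluded from Arm A only**

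Arm A has 40(1 - f) patients, and SE = sqrt[1/(40(1 - f)) + 1/40]. Power = Phi[d/SE - 1.960]. For f = 0.15: Arm A = 34, SE = 0.2333; 0.626 / 0.2333 = 2.686; Phi(0.726) = 0.766.

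**(c) Type I error under (b)**

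Suppose those who fail would score g SD worse whichever arm they are in. Arm B keeps them, so its mean is lower by f x g, and with no true effect the contrast favours Arm A by f x g. Two-sided type I error = 1 - Phi(1.960 - fg/SE) + Phi(-1.960 - fg/SE). For f = 0.15 and g = 0.5: bias = 0.075 SD; fg/SE = 0.322; result 0.062.

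| f | Power, kept (a) | Power, excluded (b) | Bias, g = 0.5 | Type I, g = 0.5 | Type I, g = 1 |
|---|---|---|---|---|---|
| 0% | 80.0% | 80.0% | 0 | 5.0% | 5.0% |
| 5% | 75.9% | 79.0% | 0.025 SD | 5.1% | 5.6% |
| 10% | 71.3% | 77.8% | 0.050 SD | 5.5% | 7.2% |
| 15% | 66.3% | 76.6% | 0.075 SD | 6.2% | 9.9% |

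**The case against.** The strongest reply is that this is an operational detail missing from a condensed article. The criterion points to the participant's own phone, applies to both arms although Arm B has no device, and contradicts nothing; the full protocol may contain a compatibility check. The cognitive, visual and language exclusions remove some unable users from both arms. Training takes place at a visit, and technical help is available afterwards. Part of this stands: the gap is narrower than the whole population of unable users, and an unpublished check is possible. But the criterion and the sequence are printed in some detail. The exclusions do not detect an incompatible phone, and a help channel cannot make one compatible.

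A second reply is that the bias comes from the 60% rule, not from the entry criterion. That is right, and a pairing check without a change to that rule would still let patients who stop wearing the watch be removed from one arm. A third is that diluted effect is what offering wearables to this population really produces. That is a fair choice of question, but it sits badly with a plan that does not keep non-users.

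Two stronger readings are tempting. A reader might infer that one-arm discovery is itself a bias; without the exclusion it is only non-adherence. A reader might also set 2.5 to 7.5 failures (5-15% of 50) against the 10 dropouts allowed per arm (50 - 40) and conclude that up to three quarters of the allowance is used up. The documents do not support this. The primary outcome is the IPAQ-SF at the six-month visit, a questionnaire that needs no phone, so a sync failure loses no outcome unless the patient is excluded.

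**Conclusion.** The point holds as a combination: an access-only criterion, a workability test in one arm after allocation, and an exclusion that only that arm can trigger. It should be corrected.

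Its size rests on assumptions. At 5-15% failure the main cost is power: about 76-66% if these patients are kept and gain nothing from the devices, which is the pessimistic case, or 79-77% if they are removed. The inflation of type I error after removal is small with a 0.5 SD gap (5.1-6.2%) and grows only with a larger gap (5.6-9.9% at 1 SD). The bias favours Arm A only if those who fail would have done worse. These figures use a comparison of means because the article gives no effect size; they show order of magnitude and do not predict this trial's results.

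**What to change.** Make two changes together.

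1. Reword the criterion along these lines: *own smartphone compatible with both device apps, confirmed for every patient by a brief staff-run compatibility and sync check before allocation is revealed, without showing activity feedback*. Withholding feedback limits exposure of future controls to the intervention.
2. Keep all randomised participants in the primary analysis regardless of device use, and report use below 60% as adherence. This removes the one-arm exclusion, which the check cannot do.

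The cost is a short extra step for each patient before allocation, a few more screen failures and a slightly less digitally naive sample. The check does not prove that a patient can manage the devices for six months; the second change deals with those who later cannot. If the full protocol already contains such a check, the article's criterion should say so.
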